## Abstract

**Background:**

Menière’s disease is an idiopathic disorder characterized by recurrent episodes of vertigo lasting more than 20 min, unilateral sensorineural hearing loss, and tinnitus. If vertigo attacks occur frequently, the patient is usually severely incapacitated. Currently, there is no consensus on the treatment of Menière’s disease. The evidence regarding most treatment options is sparse due to a lack of randomized trials together with an often-spontaneous relief over time and a considerable placebo effect. Insertion of a transmyringeal tube is a simple and relatively safe, minimally invasive procedure and previous open-label trials have shown promising results.

**Study design:**

This is a prospective, sham-controlled, double-blinded, randomized, clinical trial.

**Aim:**

This trial aims to assess the effects of inserting a ventilation tube into the tympanic membrane compared with sham treatment for definite or probable unilateral Menière’s disease according to the criteria formulated by the Classification Committee of the Bàràny Society.

**Outcomes:**

The primary outcome will be the number of spontaneous vertigo attacks lasting more than 20 min and time to treatment failure. In addition to the primary outcome, we will assess various secondary outcomes related to hearing, ear fullness, dizziness, and serious adverse events.

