### Outcomes

#### Primary outcome (main study 3 months)

The number of spontaneous vertigo attacks lasting more than 20 min during the study period will be compared between the two study groups.

This outcome was chosen as vertigo is the most disabling symptom of Menière’s disease.

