#### Primary outcome (the extended study of up to 24 months)

Time to treatment-failure will be compared between the two study groups and presented as a Kaplan-Meier plot.

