**Timeline:**

t_1_: At one month

t_2_: At two months

t_3_: At three months

t_4_: At three to six months from t_3_

t_5_: At three to six months from t_4_

t_6_: At three to six months from t_5_

t_7_: At three to six months from t_6_

t_8_: At three to six months from t_7_

t_9_: At three to six months from t_8_

^a^Patients will be asked to fulfill a weekly subjective symptom score-scheme regarding dizziness, tinnitus, hearing and aural fullness.

The participants will then be asked if they want to participate in a follow-up study which entails a follow-up every 3 to 6 months for a maximum of 24 months.

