### Sample size

The primary outcome in the study will be the number of attacks within the first 3 months after ventilation tube insertion. Because this is count data (i.e. an incidence rate) a Poisson distribution is expected, and a Poisson regression model most likely will give the best fit for analysis of the primary outcome.

The simulation software ”Powersim” developed for the used statistical package, STATA, was applied for Power calculations.

Given the lack of published data concerning the expected effect of ventilation tube insertion, we chose to assume a 50% reduction in the intervention group, which we believe is realistic as well as a necessity. A 50% reduction gives an Incidence Rate Ratio (IRR) of 0.5 and an ln(IRR) of −0.69315.

Using an alpha value of 0.05 and an expected effect size of 0.5 (ln(0.5) = −0.69315), and to obtain a power of 0.8, an expected 94 participants in total or 47 participants in each group will be necessary. To adjust for drop-outs, a safety margin of 10% results in 104 participants in total.

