#### Functional level scale

The AAO-HNS functional level scale (see Additional file 1: Appendix 5.1) consists of written descriptions of how Menière’s disease affects the life of the participants, from no impact at all (level 1) to handicapped and unable to work (level 6). The participant chooses the description that fits best. The form will be filled out at inclusion and after 3, 6, 12, 18, and 24 months.

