### Statistics

The intervention group and the control group will be compared concerning all outcomes based on the intention-to-treat principle. That is, all participants will be analysed in the groups to which they were randomized, regardless of whether they adhered to the allocated intervention.

In general, count data will be analysed using Poisson regression, continuous data with mixed linear modelling, and binary data with logistic regression. For the speech audiometry, we plan to dichotomize the data into an ≥8% decrease or not, to be able to apply logistic regression. For the AAO-HNS Functional Level Scale, we plan to dichotomize the outcome into a change ≥2 or not, for the same purpose.

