#### Outcomes

**Table Tabb:** 

**Primary outcome**	**Type of data**	**Analysis**
Number of spontaneous vertigo attacks lasting more than 20 min	Count	Poisson-regression

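### Time to treatment failure is labelled primary beside the 3-month attack count, but the sizing, the primary-outcome table and the superiority rule do not cover it, and its time origin and handling of those who decline the extension are unstated

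*Protocol article*

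**What the plan says.** The abstract puts two outcomes under one label: "The primary outcome will be the number of spontaneous vertigo attacks lasting more than 20 min and time to treatment failure". In the body, the heading for the 3-month main study assigns the attack count ("The number of spontaneous vertigo attacks lasting more than 20 min during the study period will be compared between the two study groups"). A second primary-outcome heading, for the extended study, assigns the other: "Time to treatment-failure will be compared between the two study groups and presented as a Kaplan-Meier plot".

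Elsewhere only the count appears. The Sample size section says "The primary outcome in the study will be the number of attacks within the first 3 months after ventilation tube insertion", and the primary-outcome table under Statistics has one row, the attack count with Poisson regression. The superiority rule, given under Trial design and again under Analysis population and missing data, requires superiority in the intention-to-treat set. It does not name the outcome.

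On follow-up after month 3, the Participant timeline says: "The participants will then be asked if they want to participate in a follow-up study which entails a follow-up every 3 to 6 months", up to a 24-month maximum. The Statistics section promises an intention-to-treat comparison for every outcome, in all participants as randomised. Leaving because of treatment failure in the first 3 months is a separate secondary outcome.

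**The concern.** A trial with two outcomes called primary needs a rule for combining them: either may succeed, both must, or one comes first. This plan has none. If the attack count is null and the 24-month curve favours the tube, the abstract supports a claim of superiority, while the sample size and the outcome table do not.

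The 24-month comparison has a second weakness. Participants decide whether to continue after three months' experience of their treatment. The Modifications section reminds unsatisfied participants that they may drop out. If the decision to continue is related to how the patient is doing, those followed to 24 months are no longer the randomised groups, and censoring the rest at month 3 may be informative. An explicit statement of the analysis population, time origin and handling of decliners would contain this, and none is given. The trial's own rationale cites a recommendation of at least 2 years' follow-up, so readers will look to this comparison for the long-term effect.

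**Working it through.** **1. Which outcome is primary, place by place**

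| Place | Primary outcome |
|---|---|
| Abstract, Outcomes | Attack count and time to failure |
| Outcomes, main study | Attack count |
| Outcomes, extended study | Time to failure |
| Sample size | Attack count, first 3 months |
| Statistics, primary-outcome table | Attack count only |
| Trial design; Analysis population | Superiority in the intention-to-treat set, no outcome named |

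**2. The plan's own figure.** Inputs from Sample size: IRR 0.5, alpha 0.05, power 0.80. The control mean μ0 (attacks per 3 months) is not given. The Wald formula is n per arm = (1.960 + 0.842)² × (1/μ0 + 1/(0.5 μ0)) / (ln 0.5)². With μ0 = 1 assumed, 7.849 × 3 / 0.4805 = 49.0. Other standard variants give 45.2 to 47.1, and simulated power at 47 per arm is 0.803. With μ0 = 0.5 the formula gives 98, and with μ0 = 2 it gives 24.5. So 47 per arm is reproduced if μ0 is about 1. For drop-out, 94 × 1.10 = 103.4, rounded up to 104. No input concerns time to failure.

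**3. Error rate under an either-outcome rule.** For two independent tests at 0.05, 1 − 0.95² = 0.0975. Positive correlation between the outcomes would lower this. Splitting alpha to 0.025 each multiplies the count's sample size by (2.241 + 0.842)² / (1.960 + 0.842)² = 1.211. That gives 47 × 1.211 = 56.9, so 57 per arm, or 114 before drop-out against 94. Keeping 47 per arm at 0.025 leaves power of 0.71.

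**4. What 104 participants could show on time to failure.** Schoenfeld: events = 4 × (1.960 + 0.842)² / (ln HR)². HR 0.5 needs 66 events (71 by Freedman), HR 0.6 needs 121 (126) and HR 0.7 needs 247 (253). At HR 0.5 that is 66/104 = 63% to 71/104 = 68% of everyone failing under complete follow-up.

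The documents give no hazard ratio, failure rate or opt-in rate. The table shows assumed ranges: expected events among those who continue, and power at HR 0.5.

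| Opt-in | 30% fail | 50% fail | 70% fail |
|---|---|---|---|
| 100% | 31 events, 0.49 | 52, 0.71 | 73, 0.84 |
| 80% | 25, 0.41 | 42, 0.61 | 58, 0.75 |
| 60% | 19, 0.32 | 31, 0.49 | 44, 0.63 |
| 50% | 16, 0.28 | 26, 0.42 | 36, 0.55 |

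Put the other way, HR = exp(−2 × 2.802 / √events): 80% power needs HR 0.46 with 52 events and HR 0.37 with 31.

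**5. Who is in the 24-month analysis.** The extended-study paragraph sets no time origin. Failures in months 0 to 3 are recorded, but as a separate secondary outcome, with no statement that they are events in the curve. Nothing says whether decliners are censored, excluded or otherwise handled. Under Retention, permission to keep recording data is sought from those who drop out after month 3. Those who drop out earlier are asked only for a functional level scale.

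**6. Extension intervals.** The timeline lists six visits, t4 to t9, each 3 to 6 months after the last. They end between 3 + 6 × 3 = month 21 and 3 + 6 × 6 = month 39. Counting the 24-month maximum from randomisation, six visits fit only if the mean interval is at most (24 − 3)/6 = 3.5 months. Retention says every third month, which gives (24 − 3)/3 = 7 occasions, not six.

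**The case against.** The strongest reply is that the body separates the two outcomes by stage. One primary heading is tied to the 3-month main study and the other to the extension. The sample size speaks of the count as the study's primary outcome, and the planned interim analysis of a single primary endpoint after 3 months' follow-up fits only the count. This stands in large part. What remains is the abstract's joint label, the second primary heading, and a superiority rule that names no outcome.

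Four stronger readings are tempting, and the document does not support them:

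- **That the false-positive risk is 9.75%.** This needs a rule that either outcome may claim success, and no section states one. If both had to succeed, or each stage answered its own question, the figure would not apply.
- **That the curve starts at month 3 in volunteers.** No section sets that origin. Intention-to-treat is promised for all outcomes and early departures for failure are recorded, so a curve from randomisation is possible. The defect is that it is not specified.
- **That declining is linked to failure.** This is plausible but not shown; patients who are doing well may also decline.
- **That a Kaplan-Meier plot is the whole analysis.** The text says the groups will be compared. The Statistics section gives methods by data type ("count data will be analysed using Poisson regression, continuous data with mixed linear modelling, and binary data with logistic regression") and none for time-to-event data, but the test, the effect measure and the definition of failure may sit in the unseen analysis plan. They are not counted here.

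The times for the functional level form ("The form will be filled out at inclusion and after 3, 6, 12, 18, and 24 months") concern that form and are not a rival visit schedule. The 39-month end is already excluded by the stated maximum, and no section says that failures are dated by clinic visit. The power table rests on assumed inputs, and an unsized extension outcome is common.

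**Conclusion.** The point holds as a contradiction over which outcome is primary, together with an under-specified 24-month comparison. The sections do not agree on the primary outcome, and as written a positive 24-month curve with a null attack count could be presented as superiority. The error rate is up to 9.75%, conditional on an either-outcome rule and independent tests. The 94/104 figure supports the count alone, on an assumed control mean of about 1. For time to failure at HR 0.5, power over the assumed ranges runs from 0.28 to 0.84, which illustrates that the outcome is unsized and is not an estimate.

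Selection and informative censoring after the month-3 opt-in are risks left open by silence on origin, early failures and decliners. They are not demonstrated biases. The 3-month attack-count comparison is unaffected by the opt-in.

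**What to change.** - **Primary outcome.** Name the 3-month attack count as the sole primary outcome in the abstract, in both statements of the superiority rule, and by relabelling the extended-study heading. The sample size and primary-outcome table already agree with this.
- **Time to treatment failure.** Make it a key secondary outcome, tested only if the primary is significant. No alpha split is then needed and N stays at 94, or 104 with the drop-out margin.
- **Its analysis.** Include all randomised participants from randomisation, count failures in the first 3 months as events, and censor decliners at last contact. That censoring may itself be informative, so add a sensitivity analysis treating decliners as failures, and report the number declining by arm.
- **Intervals.** Reconcile the extension follow-up in the Participant timeline (every 3 to 6 months, t4 to t9, 24-month maximum) with Retention (every third month).

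The cost is wording and a protocol amendment, and the 24-month result loses primary status. Seeking decliners' failure status from records would strengthen the analysis but is optional. Enrolment began in October 2021, so it would need an ethics amendment and re-consent of those already enrolled.

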**Sample size:**

An estimated 104 participants in total or 52 participants in each group will be necessary.

The primary analysis will be according to the intention-to-treat principle. The trial will be initiated in 2021 and is expected to end in 2025.

**Trial status:**

ClinicalTrials.gov: NCT04835688. Registered on April 8, 2021.

Protocol version: 1.8, 26-09-2022. Date of first enrollment: October 1st, 2021. End of study: anticipated January 2025.

**Supplementary Information:**

The online version contains supplementary material available at 10.1186/s13063-022-06777-w.

## Introduction

### Background information and rationale

Menière’s disease is an inner ear disorder with recurrent attacks of vertigo, fluctuating sensorineural hearing loss, tinnitus, and aural fullness [1]. The underlying pathogenetic mechanisms are not known. The pathologic-anatomic correlate of the disease is endolymphatic hydrops, i.e. distension of the endolymphatic spaces as seen at post-mortem microscopic examination of the temporal bone. Prevalence figures are in the range between 0.1 and 0.5% in the population [2, 3]. In Denmark, the estimated prevalence of Menière’s disease is 3500 [4]. The disease commonly begins in the fourth or fifth decade of life, and the prevalence increases with age [5].

There are a great number of different treatment options for Menière’s disease including diuretics, sodium restriction, beta-histidine, and psycho-supportive means, most of which are not validated [6]. The only validated treatment for vertigo attacks is chemical labyrinthectomy by intra-tympanic injections of the ototoxic antibiotic gentamicin for which two double-blind, placebo-controlled trials found a significant effect [7, 8]. Treatment with gentamicin is ablative, i.e. the goal of the treatment is to destroy the vestibular sensors of the affected ear. This carries a risk of long-standing unsteadiness alongside a permanent hearing loss in the treated ear. Still, no treatments seem to protect from the hearing loss associated with Menière’s disease.

The first to advocate the use of transmyringeal ventilation tubes for Menière’s disease was Tumarkin in 1966 [9]. Tumarkin et al. suggested that negative middle-ear pressure, due to poor tubal function, would lead to a relative over-pressure in the inner ear and that this might be one of the mechanisms behind Menière’s disease. Also, Tumarkin et al. presented several cases where treatment with transmyringeal tubes resulted in relief from vertigo attacks. Hall and Brackmann performed tympanometry in patients with Menière’s disease and showed that some, but not all, patients had negative middle-ear pressure and they questioned Tumarkin’s suggestions [10]. Recent results from Brattmo et al. on long-term measurement of middle-ear pressure and tubal function showed that a majority of patients with Menière’s disease have a poor tubal function [11].

#### Choice of comparator

Open-label trials have shown promising results with about 80–90% of the patients showing significant relief from vertiginous spells during treatment with transmyringeal tubes. In one randomized, single-blinded, controlled trial the long-term effect over 12 months of transmyringeal tubes was compared to that of endolymphatic sac surgery, and no significant differences between the treatments were found [12]. Animal studies have shown that the insertion of a transmyringeal tube prevents the induction of endolymphatic hydrops after ligation of the endolymphatic duct [13]. However, the placebo effect associated with MD treatment is generally considered to be substantial. Therefore, we find it relevant to do a sham-controlled trial. When planning a randomized clinical, placebo-controlled trial, AAO-HNS recommends having a follow-up time of 2 years or more [14].

Every year, a lot of children in Denmark and Sweden are treated with transmyringeal tubes to prevent acute purulent otitis media and to relieve conductive hearing loss due to secretory otitis media. An unknown number of tubes are inserted in adults because of secretory otitis media, tuba aperta, and to treat Menière’s disease. Tube insertion in adults is usually easily performed as an office procedure under topical or local anaesthesia. The main complications from ventilation tubes are purulent otitis media while the tube is in place and persistent perforation after tube extrusion.

### Objectives

#### Main objective

The main objective of the trial is to assess the effects of transmyringeal ventilation tubes compared with sham treatment which does not ventilate the middle ear.

#### Research hypothesis

Insertion of a ventilation tube does have an impact on vertigo attacks in patients with Menière’s disease.

### Trial design

The design is a parallel, prospective, sham-controlled, double-blinded, randomized, clinical trial.

We plan to test superiority using the intention-to-treat set. We propose declaring surgical management superior to sham treatment, only if shown to be superior using the intention-to-treat analysis set.

## Methods: participants, interventions, and outcomes

We used the SPIRIT reporting guidelines when developing the protocol [15]. A flow diagram for the study can be found in the Additional file 1: Appendix.

### Study setting

The study will be conducted at an estimated 40 private-practising ear, nose, and throat-clinics (ENT-clinics) in Denmark and Skåne University hospital in Sweden.

### Eligibility criteria

#### Study subjects

A minimum of 94 participants with definite or probable unilateral Meniére’s disease will be enrolled according to the criteria formulated by the Classification Committee of the Bàràny Society. But to get safety margins and account for drop-outs, we have decided to enrol a total of 104 consecutive participants.

#### Inclusion criteria

Participants aged 18 years or older with definite or probable unilateral Menière’s disease according to the diagnostic criteria formulated by the Classification Committee of the Bárány Society, The Japan Society for Equilibrium Research, the European Academy of Otology and Neurotology (EAONO), the Equilibrium Committee of the American Academy of Otolaryngology – Head, and Neck Surgery (AAO-HNS), and the Korean Balance Society [16]:A.Two or more spontaneous episodes of vertigo, each lasting 20 min to 12 hB.Audiometrically documented low- to medium-frequency sensorineural hearing loss in the affected ear on at least one occasion before, during, or after one of the episodes of vertigoC.Fluctuating aural symptoms (hearing, tinnitus, or fullness) in the affected earD.Not better accounted for by another vestibular diagnosis

Furthermore, the patient must have experienced at least two vertigo attacks during the last 3 months before inclusion.

In probable Menière’s disease, the diagnostic criteria cover the same points (A, C, D). However, episodes of vertigo or dizziness may last from 20 min to 24 h [17]. Furthermore, the patients must have experienced at least two spontaneous vertigo attacks lasting more than 20 min during the past 3 months [16].

#### Exclusion criteria

Bilateral Menière’s diseasePrevious treatment with transmyringeal ventilation tubes after childhoodPrevious ablative or surgical therapy, such as intratympanic gentamicin or endolymphatic sac surgeryExpected problems to adhere to the study protocol (dementia, non-fluent in Danish, substance abuse, etc.)

### Interventions

#### Description

The participants will be divided randomly into two intervention arms, an experimental group, and a control group. The procedures are described below.

In both groups, the tympanic membrane will be anaesthetized by local application of topical prilocaine (EMLA) or phenol or by infiltration anaesthesia of the outer ear canal. The choice of method is left to the ear, nose, and throat specialist (ENT specialist).

For the experimental group, insertion of a ventilation tube will be performed. An incision is performed, usually in the lower, anterior quadrant of the tympanic membrane, and the transmyringeal tube is inserted. This procedure is usually painless and well-tolerated.

For the control group, the ENT specialist will touch the tympanic membrane with an alligator ear forceps to simulate getting a paracentesis. In the same procedure, a ventilation tube is placed on the tympanic membrane and removed again afterwards without having made a paracentesis. The reason for the above-mentioned is to simulate getting a paracentesis and insertion of a ventilation tube.

The interventions will be performed after the participant has been included in the trial. To improve adherence to the intervention, the position of the tube will be inspected once every month for the first 3 months. This is to avoid spontaneous extrusion of the tube.

If the tube is spontaneously extruded, a new ventilation tube insertion will be performed. In the same way, if a patient with a sham intervention thinks that the tube has spontaneously extruded, then a new sham procedure will be performed.

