#### Secondary outcomes (main study 3 months)

The secondary outcomes of this study are comparisons between the two study groups regarding:Pure-tone audiometry of affected ear, four-tone average of 500, 1000, 2000, and 3000 Hz (dB)Pure-tone audiometry of affected ear, three-tone average of 125, 250, and 500 Hz (dB)Speech audiometry of affected ear, discrimination (%)AAO-HNS Functional level scale (1–6)Subjective hearing (0–10 arbitrary scale)The subjective intensity of ear fullness/pressure (0–10 arbitrary scale)The subjective intensity of dizziness/unsteadiness (0–10 arbitrary scale)The subjective intensity of tinnitus (0–10 arbitrary scale)Need of “escape medication”Number of subjects leaving the study because of treatment failureNumber of subjects satisfied with the treatmentSerious adverse events (as defined by the ICH-GCP)

These outcomes were chosen to assess any possible effects of treatment on hearing, functional level, and subjective symptoms.

The number of vertigo attacks, need for escape medication, and level of subjective symptoms will be recorded weekly by the study subject on a standardized form. Hearing tests will be performed at inclusion and after 3 months. A tympanometry will be performed after 1, 2, and 3 months. Assessment of AAO-HNS functional level scale will be made at inclusion and after 3 months. Menière’s disease staging (I–IV) will be decided at inclusion. Four-tone average of worst audiogram during the last 6 months: < 26 dB = Stage 1, 26–40 dB = Stage 2, 41–70 dB = Stage 3, > 70 dB = Stage 4. The equipment for hearing tests is maintained and calibrated by each study centre.

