#### Concealment mechanism

Participants will be randomized using REDCap, a web-based randomization service. The allocation concealment will be ensured, as the service will not release the randomization code until the patient has been recruited into the trial, which takes place after all baseline measurements have been completed in the RedCap system.

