#### Implementation

The statistician will generate the allocation sequence. The ENT specialists will screen and obtain informed consent. The ENT specialist will be given a direct phone number to a project nurse who will perform the registration and randomization of the participant.

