### Blinding

#### Masking

Participants, care providers, data collectors, outcome assessors, research personnel, and data analysts will be blinded to treatment allocation. However, the ENT specialist performing the insertion of the ventilation tube or sham treatment will inevitably be aware of treatment allocation.

At the end of the final visit, the participants will be asked what treatment they believe to have received. This will enable an assessment of the adequacy of blinding.

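### The anaesthetic is chosen freely by an operator who knows the allocation, so the method could differ between tube and sham

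*Protocol article*

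**What the plan says.** Under Interventions, Description, both groups receive anaesthesia of the eardrum by topical prilocaine, phenol, or infiltration of the outer ear canal. The selection is discretionary: "The choice of method is left to the ear, nose, and throat specialist (ENT specialist"). The experimental group then has an incision and a tube. The control group has the membrane touched with forceps and a tube laid on it and removed, with no incision.

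The same section provides for repeat procedures. An extruded tube is replaced, and "if a patient with a sham intervention thinks that the tube has spontaneously extruded, then a new sham procedure will be performed". Neither provision mentions the anaesthetic.

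Under Masking, participants and outcome assessors are to be blinded, with one exception: "However, the ENT specialist performing the insertion of the ventilation tube or sham treatment will inevitably be aware of treatment allocation".

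Under Implementation, "The ENT specialist will be given a direct phone number to a project nurse who will perform the registration and randomization of the participant". Under Concealment mechanism, "the service will not release the randomization code until the patient has been recruited into the trial", which happens once baseline measurements are complete. The anaesthetic method is not mentioned in either section.

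**The concern.** The sham is meant to make the two procedures indistinguishable to the participant. The reason is given under Choice of comparator: "the placebo effect associated with MD treatment is generally considered to be substantial". The anaesthetic is part of what the participant experiences, yet it is selected by the one person who may already know the arm.

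There is an ordinary clinical motive to adapt it. One procedure cuts the eardrum and the other only touches it. A considerate specialist might give infiltration for the first and something lighter for the second. If that happens often, the arms differ in anaesthetic as well as in ventilation.

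The outcomes are exposed to such a difference because attacks, escape medication and symptom levels "will be recorded weekly by the study subject on a standardized form". What participants expect or suspect can therefore enter the primary count directly.

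**Working it through.** **Text check.** Four points settle whether an arm-related choice is possible.

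1. *Who chooses?* The ENT specialist, with no stated constraint (Description).
2. *Does the chooser know the arm?* Yes, as the operator (Masking).
3. *Must the choice precede the code?* No such rule appears under Description, Sequence generation, Concealment mechanism or Implementation. The order of anaesthesia and randomisation at the first procedure is left open, so the choice may come first in practice, but nothing requires it.
4. *Is the first method kept at a repeat?* No such rule appears. An operator who did the first procedure already knows the arm by then.

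Specialists who always use one method are balanced by randomisation, apart from chance. Only those who adapt the method to the procedure can create a systematic difference.

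**Possible size.** The plan has no figure to reproduce, and every input below is an assumption. Let r be the proportional fall in reported attacks associated with one method (negative for a rise), and let p_tube and p_sham be the proportions receiving it. With a tube that has no effect, the apparent ratio is

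IRR = (1 − r·p_tube) / (1 − r·p_sham)

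| p_tube v p_sham | r | Calculation | IRR |
|---|---|---|---|
| 50% v 20% | 0.2 | 0.90 / 0.96 | 0.938 |
| 50% v 20% | 0.1 | 0.95 / 0.98 | 0.969 |
| 50% v 20% | −0.1 | 1.05 / 1.02 | 1.029 |
| 50% v 20% | −0.2 | 1.10 / 1.04 | 1.058 |
| 80% v 20% | 0.2 | 0.84 / 0.96 | 0.875 |
| 80% v 20% | −0.2 | 1.16 / 1.04 | 1.115 |
| equal use | any | – | 1.00 |

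The Sample size section assumes an IRR of 0.5, that is, ln(0.5) = −0.693. For the 50% v 20% case with r = 0.2, ln(0.938) / ln(0.5) = 0.065 / 0.693 ≈ 0.093, or about 9% of the design effect on the log scale.

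**Would a table reveal it afterwards?** Take 52 per arm, a two-sided 0.05 level and a z-test using the pooled standard error. Both splits below have a pooled proportion of 0.35, so the chance SD of the difference is √(2 × 0.35 × 0.65 / 52) = 0.094.

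- 50% v 20%: z = 0.30 / 0.0935 = 3.21. With the SD under the alternative √((0.25 + 0.16) / 52) = 0.089, power is Φ((0.30 − 1.96 × 0.0935) / 0.089) ≈ 0.91.
- 40% v 30%: with the SD under the alternative √((0.24 + 0.21) / 52) = 0.093, power is Φ((0.10 − 1.96 × 0.0935) / 0.093) ≈ 0.19.

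A table would usually expose a large split and usually miss a modest one.

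**The case against.** The strongest reply is that nothing here is wrong on its face. Anaesthesia is mandatory in both arms from one identical list, and leaving a routine choice to the clinician is reasonable across about 40 private practices. A REDCap field or the script of a telephone call is the kind of operational detail that a journal article leaves to the full protocol or site instructions. Any method is allowed in either arm and each participant sees only one procedure, so the method alone does not reveal the allocation. No passage shows that specialists adapt the method, or that doing so would change three months of attack counts. The effect sizes above are invented, and even so they are small. The lack of an incision in the sham is probably a larger threat, and the proposed change does not touch it. Finally, blinding is checked: "At the end of the final visit, the participants will be asked what treatment they believe to have received".

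Most of this stands as a limit on size. The bias is hypothetical, its direction is unknown, and the figures are only illustrative. It does not remove the point. The free choice and the operator's knowledge of the arm are both stated in the article, and the weakness lies in their combination. A shared list ensures that both arms receive some anaesthetic, not the same mix. The treatment guess can reveal that blinding failed but cannot prevent it, and without method by arm it cannot show whether the anaesthetic contributed.

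**Conclusion.** The concern holds as a minor design weakness. As written, the rule lets an operator who knows the allocation choose a part of the procedure that the participant experiences, at the first procedure possibly and at a repeat by the same operator certainly. Whether the arms will in fact differ cannot be established from the documents, nor can the direction or size of any resulting bias.

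Under the assumed 50% v 20% split and a 20% change in reported attacks either way, the distortion of a null result is an IRR of 0.94 to 1.06. It widens to 0.88 to 1.12 at 80% v 20% and vanishes if use is equal. None of these approaches the design IRR of 0.5. The case for acting is that prevention is nearly free, while later tabulation would often miss a modest imbalance.

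**What to change.** For participants still to be randomised, keep all three methods and the specialist's freedom to choose among them, but take the choice before the allocation is known:

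- The specialist names the intended method during the existing call to the project nurse.
- The nurse enters it as a mandatory REDCap field before the code is released. The system already withholds the code until baseline is complete.
- That method is used in whichever arm is drawn, and again at any repeat tube or sham procedure.
- Departures are recorded with the reason.
- Method is tabulated by arm alongside the end-of-study treatment guess.

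The cost is one field and one question, with no added staff or procedure. Two limits remain. A method may occasionally have to change at the chair after allocation is known, which is why departures need recording. Participants treated since enrolment began in October 2021 are not covered.
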